## Abstract

**Background:**

High Dose Rate Brachytherapy (HDRB) boost is a well-established treatment for prostate cancer (PC). We describe the PROstate Multicentre External beam radioTHErapy Using Stereotactic boost (PROMETHEUS) study. Non-surgical stereotactic techniques are used to deliver similar doses to HDRB boost regimens with a dose escalation sub-study.

**Methods:**

Eligible patients have intermediate or high risk PC. PROMETHEUS explores the safety, efficacy and feasibility of multiple Australian centres cooperating in the delivery of Prostate Stereotactic Body Radiotherapy (SBRT) technology. A SBRT boost component Target Dose (TD) of 19Gy in two fractions is to be delivered, followed by a subsequent EBRT component of 46Gy in 23 fractions. Once accrual triggers have been met, SBRT doses can be escalated in 1 Gy increments to a maximum of 22Gy in two fractions. Patient safety will also be measured with the rate of both acute and late moderate to severe Gastro-Intestinal (GI) and Genito-Urinary (GU) Common Terminology Criteria for Adverse Events (CTCAE) toxicities as well as patient reported quality of life. Efficacy will be assessed via biochemical control after 3 years.

**Discussion:**

PROMETHEUS aims to generate evidence for a non-surgical possible future alternative to HDRB boost regimens, and introduce advanced radiotherapy techniques across multiple Australian cancer centres.

**Trial registration:**

The study was retrospectively registered on the ANZCTR (Australian New Zealand Clinical Trials Registry) with trial ID: ACTRN12615000223538.

## Background

Prostate Cancer (PC) is a common malignancy in Australian men. In men with localized disease, external beam radiotherapy (EBRT) is a regularly used management option.

Conventional fraction sizes of 1.8–2 Gy per day are considered to be a standard treatment approach. There is, however, a growing body of evidence to support the efficacy and safety of larger doses per fraction [1–3]. This stems from clinical radiobiological data suggesting that PC has a low alpha/beta ratio (ABR), and as such a therapeutic ratio could be exploited between the differential fraction size sensitivity of the prostate and the adjacent critical structures, especially the rectum [4, 5].

A fundamental concept in radiation oncology is that Tumour Control Probability (TCP) increases as a function of radiation dose. This principle has been validated in several randomized trials of EBRT, with all studies demonstrating an improvement in Prostate Specific Antigen (PSA) control Biological Non-Evidence of disease (bNED) [6, 7]. However, this increased efficacy came at the cost of increased late rectal toxicity [8], and has spurred the development of new technologies to escalate dose to the prostate, while sparing neighbouring critical structures.

Brachytherapy has a history spanning over two decades as one method of escalating dose to the prostate. Being surgically implanted into the prostate, brachytherapy is an extremely conformal treatment approach, allowing radiotherapy dose to be tailored very precisely to the required volume. Either Low Dose Rate Brachytherapy (LDRB) or High Dose Rate Brachytherapy (HDRB) can also be combined with 45–50 Gy of conventionally fractionated EBRT as a dose escalation strategy. Data has been published from several Australian centres confirming the feasibility, efficacy, and low rectal toxicity associated with a HDRB approach [9, 10].

Despite this evidence, brachytherapy dose escalation is only available in a relatively limited number of cancer hospitals in Australia. This is mainly due to the need for specialised personnel, theatre access, concerns regarding urethral stricture rates and the high cost of maintaining a HDRB unit [9].

All radiotherapy centres in Australia have the capacity to deliver escalated doses of radiotherapy of 76 Gy or higher. To do this safely, newer technologies have been widely introduced over the last decade. Three Dimensional (3D) planning techniques permit more detailed anatomical information to be incorporated into the design of a patient’s treatment. Image Guided Radiotherapy (IGRT) allows more precise delivery of radiation dose to the prostate [11]. Intensity Modulated Radiotherapy (IMRT) using dynamic beam shaping and inverse planning approaches facilitates shaping the higher doses of radiation to irregular shapes [12]. The combination of all of these techniques has led to reduced rates of late grade 2–3 rectal toxicity in the dose escalated setting from 26% reported in the most mature of the randomized studies [6] to ~ 6% in single institution reports [13]. As a result, these approaches feature in current Australasian guidelines and are now widely practiced in Australia [4].

Despite recent advances, it is likely that we are reaching a threshold effect with EBRT alone.

The highest reported conventional doses delivered are 86.4 Gy in 1.8 Gy fractions from MSKCC [14]. Retrospective comparison of this regimen with brachytherapy boost alternatives showed markedly inferior biochemical and metastatic disease control [15]. Advances in EBRT including IMRT and IGRT, as well as emerging evidence for hypofractionation in PC have opened up an avenue to explore Stereotactic Body Radiotherapy (SBRT) as an alternative to HDRB as a prostate radiation dose escalation strategy.

## Methods/Design

PROMETHEUS is a Phase 2 multicentre clinical trial exploring a stereotactic Radiotherapy Boost to the prostate with fractionated external beam radiotherapy. We aim to test the following hypotheses; (1) That radiotherapy dose escalation to the prostate via a SBRT boost is safe using a linear accelerator in the multi-centre setting. (2) That radiotherapy dose escalation to the prostate via a SBRT boost can be increased in a stepwise manner and finally, (3) that radiotherapy dose escalation to the prostate via a SBRT boost is feasible using a Linear Accelerator in the multi-centre setting. The study design is shown in Fig. 1.

**Fig. 1 Fig1:**
[figure not shown]
PROMETHEUS trial study design

### Key selection criteria

#### Inclusion criteria

Men capable of giving informed consent with a histological diagnosis of intermediate or high risk prostate adenocarcinoma as defined by any one of: a) Baseline PSA 10–20, Gleason grade 7 disease, Clinical stage T2b-c OR b) Baseline PSA ≥20 Gleason grade 8–10 disease, Clinical stage T3. Once deemed eligible, recommended 6 months Androgen Deprivation Therapy (ADT) for unfavourable intermediate risk or low-high risk men (1 high risk factor), and 18–24 months for men with multiple high risk factors.

#### Exclusion criteria

Patients having received previous pelvis radiotherapy, ECOG performance status > 1, hip prosthesis in-situ, inability to have a Magnetic Resonance Imaging (MRI), clinical stage T4 disease, presence of inflammatory bowel disease or severe obstructive urinary symptoms, and finally an inability to meet planning objectives.

### Objectives

The primary objectives of the study are to determine the safety and efficacy of a SBRT prostate boost. Safety will be established if the cumulative rate of either acute or late GI or GU toxicity is equivalent to or less than previously reported in the HDRB or dose escalated IGRT EBRT literatures. Efficacy will be assessed via biochemical control after 3 years.

The secondary objective of the study is to ensure that the rates of grade 3 or higher acute CTCAE GI or GU toxicity does not increase with increasing dose delivery to the Clinical Target Volume (CTV).

Multicentre feasibility will be demonstrated if 3 or more centres contribute 5 or more patients to the study.

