### Data collection

Patients will be assessed at baseline, the completion of treatment, 6 weeks post treatment, and then six monthly thereafter up to 5 years. At all visits, CTCAE GI and GU toxicity will be recorded. PSA will be measured at baseline, and then at all visits following treatment. The main efficacy endpoint is bNED calculated by the Phoenix definition of nadir+ 2 [24]. Any disease relapses or initiation of salvage treatments will also be recorded. Patient related quality of life (EPIC-26), and questionnaires regarding tolerance of treatment will also be collated at baseline, end of treatment, 12 months, 36 months and 60 months.

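### Efficacy, a primary objective, has one named time point, PSA control at 3 years, which is early for men recommended 18–24 months of androgen deprivation; a 5-year estimate should be named

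*Protocol article*

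**What the plan says.** The Objectives section states: "The primary objectives of the study are to determine the safety and efficacy of a SBRT prostate boost". For efficacy it then gives the time: "Efficacy will be assessed via biochemical control after 3 years". The Abstract repeats this. Data collection gives the measure: "The main efficacy endpoint is bNED calculated by the Phoenix definition of nadir+ 2".

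The Inclusion criteria recommend 6 months of ADT for unfavourable intermediate risk or a single high risk factor, and "18–24 months for men with multiple high risk factors". No ADT is named for other intermediate-risk men. The article does not fix when ADT starts relative to radiotherapy, does not give the expected share of men with multiple high risk factors, and sets no target rate for biochemical control.

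Visits are at baseline, end of treatment, "6 weeks post treatment, and then six monthly thereafter up to 5 years", with PSA at every visit after treatment. The Sample size section places the late toxicity report at 5 years.

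**The concern.** ADT holds PSA down, so a rise of 2 above nadir is unlikely to appear until ADT has ended and testosterone has recovered. For men on the longer recommended course, much of the first 3 years is spent under suppression. A PSA-based reading then says little about whether the disease was controlled by radiotherapy, and the error runs in the favourable direction. It falls on the men whom the protocol itself places in its highest risk category.

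What is at stake is how the efficacy result can be read. ADT is recommended and not assigned, so a pooled 3-year figure depends partly on the mix of ADT durations. The only time named for a primary objective is one at which part of the population is barely observable, although PSA is collected for 2 more years.

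**Working it through.** **Inputs from the article.** Reading at 36 months (Objectives); PSA follow-up to 60 months (Data collection); ADT of 6 or 18–24 months (Inclusion criteria); n = 268 (Sample size).

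**Assumptions, not in the article.** Months of ADT given before radiotherapy, *b* = 0 to 6. Lag in testosterone recovery, *L* = 0, or 6 to 12 months. The 3-year clock starts at radiotherapy.

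**The plan's own figure.** n = (1.96/0.05)² × 0.225 × 0.775 = 1536.64 × 0.174375 = 267.95, so 268. It reproduces, but it is sized on late toxicity, so changing the efficacy time point does not alter it.

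**Months off ADT at the reading.** Time off = *t* − (*d* − *b*) − *L*, where *t* is the reading and *d* the ADT duration.

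| ADT duration | 3 y: b=0, L=0 | 3 y: b=6, L=0 | 3 y: b=0, L=6–12 | 5 y: b=0, L=0 | 5 y: b=6, L=0 | 5 y: b=0, L=6–12 |
|---|---|---|---|---|---|---|
| 6 months | 30 | 36 | 18–24 | 54 | 60 | 42–48 |
| 18 months | 18 | 24 | 6–12 | 42 | 48 | 30–36 |
| 24 months | 12 | 18 | 0–6 | 36 | 42 | 24–30 |

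With ADT starting at radiotherapy and no lag, the long-course men have 12–18 months off ADT at 3 years, or about 2–3 six-monthly PSA tests. At 5 years they have 36–42 months, or about 6–7 tests. An assumed lag of 6–12 months leaves 0–12 months at 3 years and 24–36 at 5 years.

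**Possible effect on the pooled figure (illustration only).** Take a constant failure hazard *h* = −ln(1 − F)/36, where F is the true 3-year failure proportion. Suppose ADT plus lag delays every failure in long-course men by *m* months. The pooled overstatement at 3 years is share × {F − [1 − exp(−*h*(36 − *m*))]}.

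- Example: F = 0.10, *m* = 24, share = 25%. Then *h* = 0.10536/36 = 0.00293 per month. Visible failures are 1 − exp(−0.0351) = 3.5%. The subgroup gap is 10.0 − 3.5 = 6.5 points, and the pooled gap is 0.25 × 6.5 = 1.6 points.
- Over F = 5–20%, share = 10–50% and *m* = 18–36 months, the pooled overstatement runs from 0.2 to 10 points.
- Share of long-course failures visible at 3 years: about one half (*m* = 18), one third (24) or none (36). At 5 years: 71–74%, 61–64% and 41–45%.

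If masked failures surface soon after recovery instead of being delayed by the whole of *m*, the overstatement is smaller.

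**Yardstick.** The 95% half-width at n = 268 is 1.96 × √(p(1 − p)/268): 4.8 points at 80% control and 2.6 points at 95%. The illustrated bias can be well below sampling error or above it.

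**The case against.** The strongest reply is that no stated decision turns on this number. The Objectives section sets the comparison with published brachytherapy and external beam series for toxicity only, efficacy has no success threshold, and the Discussion says severe toxicity drove the patient numbers. That stands, and it limits the consequence to how a reported estimate is interpreted.

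Next, the wording of the 3-year sentence does not rule out later estimates, and PSA runs to 5 years. This is true, but no later efficacy estimate is named.

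Third, 5 years reduces the problem without removing it. In the example above, with *m* = 24, true 5-year failure is 16.1% and visible failure 10.0%. The proportion seen rises from 35% to 62%, but the absolute gap in the subgroup is still 6.1 points. This stands too, and is why a later reading needs to be accompanied by results by ADT duration.

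Two stronger readings are tempting. A reader might infer that many men receive 18–24 months of ADT. The article only recommends that duration, for one subgroup of unstated size; men on 6 months have about 30 months off ADT at 3 years before any lag. A reader might also infer from "Any disease relapses or initiation of salvage treatments will also be recorded" that a man given salvage before nadir + 2 counts as controlled. The article says only that such events are recorded. Whether they count as failure, are censored or are ignored is not stated, and may be set out in the full protocol or SAP, which are not shown.

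**Conclusion.** The point holds for the subgroup. Phoenix control at 3 years is immature, and probably biased towards control, in men with multiple high risk factors who follow the recommended 18–24 months of ADT. They have about 12–18 months off ADT if it starts near radiotherapy, or up to about 24 if it starts 6 months earlier, less any recovery lag.

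The direction rests on ADT suppressing PSA and on men following the recommended duration. The months also depend on where the 3-year clock starts, which is not stated; counting from the end of the treatment course would move them by about 2 months.

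The size of the effect on the pooled estimate cannot be derived from the article. The illustrated 0.2 to 10 points shows that it could be negligible or material. It does not show that the trial's result will be materially overstated.

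**What to change.** In Objectives and Data collection, name 5-year biochemical control, estimated by time-to-event methods from the six-monthly PSA already scheduled, as the mature efficacy estimate. Keep the 3-year figure as an early read-out. Report both by risk group and by ADT duration received (none, 6 months, 18–24 months).

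The cost is wording and a stratified table. The mature efficacy result arrives 2 years later than the 3-year one, at the same time as the planned 5-year toxicity report. The sample size of 268, the visits and the treatment are unchanged.

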### SBRT treatment planning

CT-MRI fusion of planning scans using prostatic fiducial registration is performed.

The CTVsbrt is the prostate plus any observed extraprostatic disease, either due to T3a extracapsular extension (ECE) or seminal vesicle invasion (SVI). For SVI include disease observed on MRI only for the boost. The SBRT Planning Target Volume (PTVsbrt) expansion is 5 mm in all directions from CTVsbrt, except posteriorly where it is 3 mm.

Table 1 lists the critical structure contouring guidelines.

**Table 1 Tab1:** Critical structure contouring guidelines

Structure name	Description
Rectal Wall	Contour as a 3 mm thick wall structure from recto-sigmoid junction to lower aspect of ischial tuberosities.
Rectal Mucosa	Solid structure corresponding to the internal cylindrical space central to the inner surface of the rectal wall.
Rectum Posterior Wall	This is the most posterior 15 mm of rectal wall
Bladder	Contour the whole organ as a solid structure.
Penile Bulb	Contour from MRI.
Prostatic urethra Planning Target at Risk Volume (PRV)	Contour urinary IDC within prostate, and add 1 mm radial expansion for the PRV. If no IDC used, estimate urethral position, and add 3 mm radial expansion.
Neck of Femur	Contour the Left and Right NOF as solid structures to the level of the ischial tuberosity.

Inverse planned IMRT or related modulated dose techniques (Tomotherapy, Cyberknife [CK] or Volumetric Modulated Arc Radiotherapy [VMAT]) are required. For static field IMRT, between 5 and 8 fields recommended. Photon energies of 6–10 MV, with higher energies not recommended due to the higher potential for neutron scatter with the large daily doses. An exception is patients with large separations where 1–2 higher energy beams may be helpful in improving dose distribution, but only if all other beams are 6–10 MV. Non-coplanar beams are allowed. VMAT may provide the advantage of more rapid treatment time reducing the need for interim imaging to manage intrafraction motion.

SBRT dose constraints should be met as per Table 2:

**Table 2 Tab2:** SBRT dose constraints. (TD = Target dose)

Constraint	Per-Protocol	Minor Variation	Major Variation
CTVsbrt D98^a^	> 100% TD	95–100% TD	< 95% TD
PTVsbrt D50^a^	< 105% TD	105–110% TD	> 110% TD
PTVsbrt D90^a^	> 100% TD	95–100% TD	< 95% TD
PTVsbrt D95^a^	> 95% TD	90–95% TD	< 90% TD
PTVsbrt D99^a^	> 16 Gy	15–16 Gy	< 15 Gy
PTVsbrt Dmax to 0.1cc	< 110% TD	110–120% TD	> 120% TD
PTVsbrt Dmax	Not within a critical structure		

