Rectal Wall Dmax to 0.1cc	< 17 Gy	17–17.5 Gy	> 17.5 Gy
Rectal Wall V16 Gy	< 0.5cc	0.5-1cc	> 1cc
Rectal Wall V14 Gy	< 3cc	3-5 cc	> 5cc
Rectal Wall V12 Gy	< 30%	30–40%	> 40%
Rectal Wall V10 Gy	< 40%	40–50%	> 50%
Rectal Wall V8 Gy	< 60%	60–70%	> 70%
Rectal Mucosa Dmax to 0.1cc	< 15 Gy	15–15.5 Gy	> 15.5 Gy
Rectal Mucosa V14 Gy	< 0.5cc	0.5-1cc	> 1cc
Rectum Posterior Wall	< 8.5 Gy	8.5–9.5 Gy	> 9.5 Gy
Bladder Dmax to 0.1cc	< 110% TD	110–120% TD	> 120% TD
Bladder V19 Gy	< 10cc	10-15cc	> 15cc
Bladder V17 Gy	< 15%	15–20%	> 20%
Bladder V9 Gy	< 50%	50–60%	> 60%
Urethra PRV Dmax to 0.1cc	< 110% TD	110–115% TD	> 115% TD
Urethra PRV V105% TD	< 5%	5–15%	> 15%
Neck of Femurs Dmax to 0.1cc	< 8 Gy	8–9 Gy	9 Gy
Penile Bulb Dmax to 0.1cc (Recommended)	100% TD	100–105% TD	> 105% TD
Penile Bulb V10 Gy (Recommended)	<3cc	3-5cc	> 5cc
Intermediate Dose Spillage: ratio of volumes receiving 50% TD to 100% TD	< 4	4–5	> 5
Total Monitor Units	< 3× Dose in cGy	3–3.5× Dose in cGy	> 3.5× Dose in cGy
High Dose Conformation: Volume receiving 100% of TD divided by volume of PTVsbrt	< 1.1	1.1–1.2	> 1.2

^a^Where Urethra has been limited to 19 Gy, these volumes may exclude the urethra: eg. CTVsbrt D98 = CTVsbrt – Urethra PRV D98

Aim to encompass the entire PTVsbrt with 19Gy minimum. However, PTVsbrt coverage may be compromised posteriorly to a minimum of 16Gy only where necessary in order to meet rectal dose constraints. Aim for 16Gy isodose line to only encompass posterior PTVsbrt where there is overlap between PTVsbrt and Rectum (see Figs. 2 and 3).

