**Fig. 3 Fig3:**
[figure not shown]
Sagittal CT view of example dose distribution. Note the high dose sparing of the Urethral PRV, and posterior PTVsbrt dose compromise to meet rectal dose constraints

The mechanism for the stepwise SBRT dose escalation is as follows:

A minimum of 20 men in total are to complete treatment without > 15% suffering a grade 3 acute toxicity or any episodes of grade 4 acute toxicity at a particular dose level. The individual centre must also accrue ≥5 patients at the previous dose level prior to exploring dose escalation. Once this accrual trigger has been met, increase the dose by 1 Gy to D98% of the volume CTVsbrt minus urethral PRV. The first dose escalation will therefore be to 20 Gy. This process can be followed a maximum of three times, to a maximum CTVsbrt-Urethral PRV D98 of 22 Gy.

A credentialing “dummy run” will need to be performed on a previous patient data set to demonstrate to an external reviewer the feasibility of achieving these new dose constraints. The first three patients planned at each dose level will be subject to a real-time QA process. An external RO review of target delineation, OAR doses and plan quality shall be undertaken before any planned treatment is delivered.

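### The acute toxicity comparison across dose levels may lean towards no increase, because the planning exclusion names no dose level and can become harder to pass as dose rises

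*Protocol article*

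**What the plan says.** Objectives: the secondary aim is to "ensure that the rates of grade 3 or higher acute CTCAE GI or GU toxicity does not increase with increasing dose delivery".

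Exclusion criteria: the list ends "and finally an inability to meet planning objectives". It names no dose level and does not say whether a minor or only a major variation counts as failure.

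SBRT treatment planning: "SBRT dose constraints should be met as per Table 2". In Table 2, CTVsbrt D98 and PTVsbrt D90 and D95 are percentages of target dose (TD). All rectal limits and bladder V19, V17 and V9 are fixed in Gy. The bladder and urethral maxima are 110% of TD. There is relief at the back of the target: "PTVsbrt coverage may be compromised posteriorly to a minimum of 16Gy only where necessary in order to meet rectal dose constraints". The footnote, "Where Urethra has been limited to 19 Gy, these volumes may exclude the urethra", suggests that the table also serves the escalated levels.

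Stepwise escalation (after Fig. 3): each step is to "increase the dose by 1 Gy to D98% of the volume CTVsbrt minus urethral PRV", from 19 Gy up to 22 Gy. A level must first have at least 20 men treated, with no more than 15% having acute grade 3 and none having acute grade 4 toxicity. In addition, "The individual centre must also accrue ≥5 patients at the previous dose level prior to exploring dose escalation".

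**The concern.** A statement that toxicity does not rise with dose needs groups that are alike apart from dose. Two written rules work against that.

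- **Planning exclusion.** If it is applied at the level being planned, a man whose rectum or bladder lies close to the target can pass at 19 Gy and fail at 22 Gy. The article does not say what then happens to him.
- **Centre rule.** A centre reaches 22 Gy only after at least 3 × 5 = 15 earlier men, whereas 19 Gy contains every centre's first men.

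If hard-to-plan anatomy carries more acute risk, and if experience lowers risk, both rules push the same way and a real rise could look flat. At stake is whether 22 Gy goes forward described as no more toxic on the strength of a selected group. Men excluded without a record cannot be recovered by later modelling, so this is a matter of design as well as analysis.

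**Working it through.** **1. The plan's own sample size.** Inputs from Sample size: p = 0.225, E = 0.05. n = (1.96/0.05)² × 0.225 × 0.775 = 1536.64 × 0.174375 = 267.95, so 268, as stated. This sizes one late toxicity proportion, not the comparison of dose levels.

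**2. Does the planning test tighten?** Inputs from Table 2; limit divided by TD.

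| TD (Gy) | Rectal wall 17 Gy | Rectal mucosa 15 Gy | 19 Gy level of bladder V19 | Required CTV D98 minus 17 Gy |
|---|---|---|---|---|
| 19 | 89.5% | 78.9% | 100% | 2 Gy |
| 20 | 85.0% | 75.0% | 95.0% | 3 Gy |
| 21 | 81.0% | 71.4% | 90.5% | 4 Gy |
| 22 | 77.3% | 68.2% | 86.4% | 5 Gy |

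If minor variations are accepted (CTV D98 at 95% of TD, rectal wall at 17.5 Gy), the gap still grows: 0.95 × 19 − 17.5 = 0.55 Gy, against 0.95 × 22 − 17.5 = 3.4 Gy. The urethral and bladder maxima stay at 110% of TD and do not tighten.

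**3. How much could selection hide?** All inputs here are assumed. Let u be the share of men with tight anatomy at 19 Gy, k their relative risk, and x the fraction of them excluded at 22 Gy. Then u₂ = u(1 − x)/(1 − ux), and the true relative risk that would show as no change is [(1 − u) + uk] / [(1 − u₂) + u₂k].

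| u | k | x | Relative risk hidden |
|---|---|---|---|
| any | 1 | any | 1.00 |
| 0.1 | 2 | 0.25 | 1.02 |
| 0.3 | 2 | 0.5 | 1.10 |
| 0.3 | 4 | 0.5 | 1.24 |
| 0.3 | 4 | 1 | 1.90 |

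**4. Which analysis shows most of a real rise?** Assumed: 30% tight; risk at 19 Gy of 5% in the other men and, at three times the odds, 13.6% in tight men; odds 1.5 times higher at 22 Gy, giving 7.3% and 19.1%; half the tight men fail planning at 22 Gy.

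- 19 Gy, all men: 0.7 × 0.050 + 0.3 × 0.136 = 7.6%.
- 22 Gy, same mix: 0.7 × 0.073 + 0.3 × 0.191 = 10.9%.
- Failing men excluded: 22 Gy shows (0.7 × 0.073 + 0.15 × 0.191)/0.85 = 9.4%, so 7.6% v 9.4%.
- Failing men treated at 19 Gy, analysed by dose given (equal numbers planned at each level): 19 Gy shows (0.076 + 0.15 × 0.136)/1.15 = 8.4%, so 8.4% v 9.4%.
- The same men, analysed by level attempted: 22 Gy shows 0.7 × 0.073 + 0.15 × 0.191 + 0.15 × 0.136 = 10.0%, so 7.6% v 10.0%.

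**5. The existing limit applied at 22 Gy.** 15% of 20 is 3, so it triggers at 4 or more grade 3 events in 20. Binomial probability, grade 3 alone: 13% at a true rate of 10%, 59% at 20%, 77% at 25%.

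**The case against.** The strongest reply is that the link to risk is not shown. Tight-anatomy men treated at 19 Gy had to meet the same organ limits in Gy as everyone else. The bias needs them to carry more acute toxicity even so, and nothing in the article establishes that. This stands, and it is why the hidden effect may be nil.

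The article also softens the planning effect: a rectal displacement device is used, posterior PTV coverage may fall to 16 Gy, the urethra may be left out of the target volumes, and minor-variation bands exist. The urethral and bladder maxima scale with dose, so the argument is weaker for GU. All of this stands.

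A reader might scale a 19 Gy plan that sits at the rectal limit: 17 × 22/19 = 19.7 Gy, a major variation. That does not show that such a man would fail, because plans are inverse-optimised afresh and only CTV minus the urethral volume is escalated.

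The exclusion could also be meant for the 19 Gy base dose only, with the full protocol covering later failures. That is possible; the article does not say. One sentence would settle it.

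On experience, the dummy run and the external real-time review of the first three patients planned at each level reduce the difference. They do not change the fact that centres' first men are all at 19 Gy.

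**Conclusion.** The point holds as a caution about possible bias. Fixed-Gy organ limits, coverage that scales with TD and an exclusion tied to no level mean that the test for entry can tighten with dose; the centre rule adds experience as a second difference. The groups may therefore differ in risk, more plausibly for GI than for GU, and the raw comparison may lean towards no increase.

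A reader might go further and infer that the groups do differ and that a rise will be masked. The document does not support that: it gives no exclusion counts, does not define the tier that triggers exclusion, and offers no evidence that anatomy or experience changes acute risk. The range of 1.00 to 1.90 for the hidden relative risk rests wholly on assumed inputs.

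The escalation limits do not fill the gap. They are absolute thresholds, not a comparison between levels, and because 22 Gy is the last level, crossing them there triggers nothing as written.

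**What to change.** 1. **Exclusion.** State that it means inability to meet planning objectives at 19 Gy. A man who fails only at a higher level is treated at the highest level that meets Table 2 and stays in the study. Log the level attempted, the limit failed and the level given.
2. **Objective.** Reword it to estimate the change in acute grade 3 or higher GI and GU toxicity per 1 Gy, with a 95% CI. Analyse mainly by level attempted, with dose given as secondary: moving failing men down and analysing only by dose given would hide more of a rise than excluding them (working, step 4). Adjust for at most one or two factors, such as the man's order in his centre (first five or later). Limit any conclusion about 22 Gy to men who can be planned at 22 Gy.
3. **22 Gy.** Apply the existing limits there: after 20 men, return to 21 Gy if more than 3 have grade 3 or any has grade 4 acute toxicity.

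**Cost.** No extra patients; a little more logging and analysis. The interval will be wide. Analysis by level attempted dilutes somewhat (10.0% against 10.9% for the same mix in the illustration). The 22 Gy limit would trigger with 13% probability at a true grade 3 rate of 10%, before counting the grade 4 rule.

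### The only toxicity comparison across dose levels rests on acute grade 3+ events not rising, an endpoint probably too sparse to show a rise between 19 and 22 Gy

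*Protocol article*

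**What the plan says.** The Objectives section makes it the secondary objective that the rate of "grade 3 or higher acute CTCAE GI or GU toxicity does not increase with increasing dose delivery to the Clinical Target Volume (CTV". No margin, reference rate or measure of trend is attached. The section does not say whether GI and GU form one combined event or two separate rates.

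Dose levels run from 19 to 22 Gy in 1 Gy steps. The escalation rule (SBRT treatment planning, after Fig. 3) also uses acute grade 3 and grade 4 events, with at least 20 men completing treatment at a level before escalation.

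Table 2 sets every rectal limit at a dose in Gy, for example "Rectal Wall Dmax to 0.1cc", "Rectal Wall V16 Gy", "Rectal Mucosa V14 Gy" and "Rectum Posterior Wall". The two urethral limits, "Urethra PRV Dmax to 0.1cc" and "Urethra PRV V105% TD", are tied to the target dose (TD), as is the bladder Dmax limit. The other three bladder limits are in Gy. A footnote provides for plans in which the urethra is held at 19 Gy, and the escalated volume is CTVsbrt minus the urethral PRV.

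Data collection states: "At all visits, CTCAE GI and GU toxicity will be recorded".

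**The concern.** An objective worded as absence of an increase is easiest to meet when its endpoint hardly ever occurs. With a handful of acute grade 3+ events per dose level, a flat-looking series is the expected result whether or not toxicity rises with dose. The trial would then report that escalation to 22 Gy added no acute toxicity, and that statement would carry forward into a later trial.

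Lower-grade acute events are recorded at the same visits and should be commoner, so they would usually say more about a dose trend. The objective as worded does not use them for that purpose.

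A second, smaller issue is the combination of GI with GU. If GI events do not move with boost dose while GU events do, combining them adds noise to the comparison.

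**Working it through.** **Inputs from the protocol.** Dose levels 19, 20, 21 and 22 Gy. Total sample size 268, which reproduces from the stated formula: (1.96/0.05)² × 0.225 × 0.775 = 267.95, rounded up to 268. That figure was derived for the late grade 2–3 rate, not for the dose comparison; it serves here only as the number of men available.

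**Assumed inputs (the protocol gives none by grade and dose).** At 19 Gy: acute grade 3+ GI 2%, grade 3+ GU 2%, grade 2+ GU 20%. GI flat over dose and independent of GU. GU odds multiply by a constant odds ratio (OR) per Gy. An even split gives 268/4 = 67 men per level.

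**Expected events at OR 1.4 per Gy, 67 per level.**
- Grade 3+ GU odds at 19 Gy are 0.02/0.98 = 0.0204. Multiplying by 1.4 per step gives rates of 2.00%, 2.78%, 3.85% and 5.30%.
- Grade 3+ GI-or-GU is 1 − (1 − GU) × 0.98, giving 3.96%, 4.72%, 5.77% and 7.20%. Times 67 this is 2.7, 3.2, 3.9 and 4.8 events, about 14.5 in all.
- Grade 2+ GU odds start at 0.25, giving 20.0%, 25.9%, 32.9% and 40.7%. Times 67 this is 13.4, 17.4, 22.0 and 27.3 events, about 80 in all.

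**Power of a one-sided 5% Cochran-Armitage trend test (simulated, 67 per level).**

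| OR per Gy | Grade 3+ GI-or-GU | Grade 3+ GU alone | Grade 2+ GU |
|---|---|---|---|
| 1.2 | 11% | 13% | 42% |
| 1.3 | 16% | 20% | 68% |
| 1.4 | 22% | 30% | 87% |
| 1.5 | 31% | 40% | 96% |

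**Sensitivity to the split, at OR 1.4.**
- 20/20/20/208: 13% combined, 13% grade 3+ GU alone, 74% grade 2+ GU.
- 188/20/20/40: 25%, 35% and 88%.
- Over OR 1.2 to 1.5 and all three splits, combined grade 3+ power stays between about 6% and 33%; grade 2+ GU runs from 30% to 96%.

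**Sensitivity to the grade 2+ base rate.** At 10% instead of 20%, with 67 per level and OR 1.4, grade 2+ GU power is 73%.

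**Cross-check with two levels only.** Rates of 2% against 6%, 67 men each, one-sided 5%: power 32%. About 296 men per level would be needed for 80%.

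**How much does combining GI with GU cost?** With 67 per level and GI exactly flat, 30% falls to 22% at OR 1.4. At 20/20/20/208 there is no loss at OR 1.4 (13% both ways), and at OR 1.3 the combined endpoint does slightly better (8.7% against about 7%). If GI rises with an OR of only 1.2 per Gy (67 per level, GU OR 1.4), the combined endpoint has 32% against 30% for GU alone.

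**Table 2 limits by dose.** The per-protocol urethral Dmax limit is 1.10 × TD: 20.9 Gy at 19 Gy and 24.2 Gy at 22 Gy. The rectal wall Dmax limit stays at 17 Gy, which is 89.5% of 19 Gy and 77.3% of 22 Gy. These are ceilings, not delivered doses.

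**The case against.** **Grade 3+ is the clinical question asked.** The Discussion puts severe toxicity first in setting patient numbers, and the escalation rule is built on grade 3 and 4 events. This stands: the grade 3+ rate is a legitimate safety measure and should stay. It does not follow that failing to see a rise in so few events shows there is none.

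**The power contrast is driven by assumptions.** A 20% endpoint beats a 2% endpoint whenever both are given the same odds ratio. That is fair. If the odds ratio for grade 2+ GU is only 1.2, its power is 42%, and at 1.1 it is 18%. The low power for grade 3+ needs only that such events be rare and the dose effect moderate. The advantage of grade 2+ also needs a dose effect at that grade.

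**Lower grades are not lost, and detail may sit elsewhere.** The Abstract refers to moderate to severe acute and late toxicity, CTCAE is recorded at all visits, and a fuller plan may specify the test and separate organ reporting. That stands against any claim that data are discarded. The absence of a named test is no fault here. The point concerns the endpoint that the objective itself fixes.

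**A reader might infer from Table 2 that GI cannot respond to dose while GU must, so that the combined endpoint is the least dose-sensitive available.** The document does not support this. The urethra may be held at 19 Gy, the escalated volume leaves out the urethral PRV, and three of four bladder limits are in Gy. Rectal limits are ceilings below which delivered dose can still vary with TD. The 46 Gy EBRT component can add GU as well as GI background. On that reader's own logic, grade 3+ GI alone would be less sensitive than the combination.

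**Conclusion.** The point holds for grade, and only weakly for the combination of organ systems. The one by-dose toxicity objective relies on a severe acute endpoint that is likely too sparse to reveal a moderate rise. Under the assumed rates with 67 men per level, power is about 16–31% for odds ratios of 1.3 to 1.5 per Gy, against 68–96% for grade 2+ GU; at 1.2 it is 11% against 42%. The direction holds under both uneven splits and with a 10% grade 2+ base rate. All of these rates are assumptions.

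The loss from combining GI with GU is small. It can disappear or reverse when the split is uneven or GI rises modestly with dose, and it does not arise at all if the objective means two separate rates. Separate reporting is worthwhile for clarity, but it is not the main gain.

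The stated sample size of 268 is unaffected, and nothing here bears on the escalation rule or on any dose constraint. This should be changed, but it is an improvement in how the dose question is read rather than a flaw that invalidates the trial.

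**What to change.** In the Objectives section:

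- Keep the acute grade 3+ rate, by dose level, as the stated severe-toxicity safety measure, and say whether GI and GU are read separately or together.
- Add a dose-trend analysis of worst acute CTCAE grade (ordinal, or grade 2 or higher) over planned TD, for GU and GI separately. Report the estimate per Gy with its confidence interval.
- State that the absence of an increase will not be concluded from sparse grade 3+ counts alone. The interval should show how large a rise remains compatible with the data.

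The cost is objective and analysis wording. No new data, visits or patients are needed, because CTCAE grades are already recorded at every visit. The downside is that grade 2 events are less serious, so the trend must always be shown beside the grade 3+ rate and not in place of it.
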